##### Stage 2: difference-in-differences (DiD) analysis

The DiD method compares changes in the prevalence of people admitted to hospital over time, contrasting the group who have a C(E)TR and the group who do not have a C(E)TR and attributes the ‘difference-in-differences’ to the effect of the intervention.^14 15^ Here, we will apply the DiD model to examine the causal effect of a C(E)TR on the prevalence of psychiatric hospital inpatient status at any point over the 6 months following the C(E)TR. Propensity scores will be included as weightings in the DiD analysis, following the method proposed in Stuart (2014). The estimand will be the average effect of the treatment on the treated. This is the average effect of receiving a C(E)TR on inpatient status, in the 6 months after the C(E)TR. The data to be entered into the DiD model is considered panel data—repeated-measures data from the same patients before and after the index date—thereby strengthening the causal claim. If the DiD model described above fails to converge or if important assumptions are not met (see Online supplemental appendixAppendix), we will use the propensity scores in a logistic regression analysis, with 6-month post-index date hospital inpatient status (yes/no) as the dependent variable and group (C(E)TR intervention/control) as an independent variable.

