## Introduction

 Reducing unnecessary psychiatric hospital admissions and length of hospital stay for people with intellectual disability and autistic people has been a focus of English national health policy since the scandal of abuse and neglect of patients at Winterbourne View Hospital in 2011.^1^ The Transforming Care programme was established to improve community health and social care for people with intellectual disability and autistic people and to reduce what had generally been considered to be an over-reliance on inpatient psychiatric services.^2^ A key element of Transforming Care has been the introduction of Care (Education) and Treatment Reviews (C(E)TRs), person-centred review meetings that aim to ensure the right support is provided.^3^ A community C(E)TR should be convened when a person with intellectual disability or an autistic person living in the community is considered at high risk of admission to a psychiatric hospital, either because of mental ill-health or because of an escalation in behaviours that challenge. C(E)TRs are chaired by a health commissioner and include an independent clinical expert and an expert-by-experience, often a family carer of a person with intellectual disability or an autistic person. This panel gathers information from the individual, their families and carers, and professionals, and produces a report and action plan following the C(E)TR with recommendations (eg, input from specialist professionals or health teams, provision of additional care, use of respite services) that can enable the person to remain living safely in the community. Where admission to hospital is considered necessary, the C(E)TR panel will define the purpose of the admission and encourage early discharge planning in order to minimise the length of the hospital stay. Inpatient C(E)TRs are convened at various points of a hospital admission; the current project investigates only C(E)TRs that are held in the community.

Little formal research has been carried out on community C(E)TRs, such as who receives them and when, and how C(E)TRs may influence health service use, including admission to hospital. By understanding the demographic and clinical profile of patients who do, and do not, have a community C(E)TR, it may be possible to develop targeted interventions to improve access to community C(E)TRs and ensure the potential benefits are available to everyone.

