##### Stage 1: propensity scores

As the retrospective analysis of EHRs is not a randomised controlled study, we will employ a propensity score weighting technique to adjust for confounders in the data. Propensity scores will balance the C(E)TR and comparison groups on a set of baseline (pre-index date) characteristics.^12^ Certain characteristics may increase the probability of someone receiving a C(E)TR, and we wish to account for these in the outcome (risk of hospitalisation) model. Scores will be calculated by fitting a multivariable logistic regression model with C(E)TR status as the dependent variable.^13^ We will condition on baseline characteristics that are believed to be related to the outcome, risk of hospitalisation, and to the probability of receiving a C(E)TR (confounders), but not those that might lie on the causal pathway from receiving a C(E)TR to being admitted to hospital (mediators), that is, variables that are affected by the intervention itself. The following variables are expected to be included in the propensity score analysis: age, sex, ethnicity, marital status, sexual orientation, deprivation score, relevant diagnosis (intellectual disability with/without autism, or autism without intellectual disability) and pre-existing psychiatric diagnoses (online supplemental table 1).

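### The fallback for the primary analysis drops pre-index inpatient status, which can push its false-positive rate well above 5%

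*Protocol article*

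**What the plan says.** The main analysis (protocol article, Stage 2: difference-in-differences (DiD) analysis) is a propensity-weighted DiD on "repeated-measures data from the same patients before and after the index date". Its estimand is the average effect of the treatment on the treated (ATT).

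The same section gives a contingency rule. The trigger is: "If the DiD model described above fails to converge or if important assumptions are not met". The replacement is: "we will use the propensity scores in a logistic regression analysis, with 6-month post-index date hospital inpatient status (yes/no) as the dependent variable". The one regressor named for that model is C(E)TR group.

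Stage 1 (propensity scores) describes the score: "The following variables are expected to be included in the propensity score analysis: age, sex, ethnicity, marital status, sexual orientation, deprivation score", followed by relevant diagnosis and pre-existing psychiatric diagnoses. The section on matching a control group uses age, sex, diagnosis and similar total time under services, and requires that a control is not an inpatient on the index date. Neither section names earlier admission or pre-index inpatient status.

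The Introduction says that a community C(E)TR should be convened when a person "is considered at high risk of admission to a psychiatric hospital".

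**The concern.** In the DiD, the before-after difference removes standing differences in admission risk between the groups. The fallback gives that up and relies on propensity scores built, as far as the text shows, from demographic and diagnostic variables. Yet the exposure is triggered by perceived admission risk. This is confounding by indication, and the outcome's own baseline is the most direct measured proxy for that risk.

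The rule takes effect when the DiD has failed, possibly because the groups were not comparable over time. The text does not soften the claim at that point: the section heading still speaks of a causal effect, and the ATT remains the stated estimand. The likely bias is upward. A null intervention could seem to raise admissions, and a protective one could look neutral.

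**Working it through.** **What is fixed and what is not.** The article gives no number of C(E)TRs (it says this is unknown), admission rate, effect size or alpha for the primary analysis. There is no planned figure to reproduce. All rates, case counts and the two-sided 0.05 level below are assumptions. The true C(E)TR effect is set to zero throughout, so every rejection is a false positive. No propensity model is simulated: the imbalance shown is whatever is assumed to remain after weighting.

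**Step 1: residual odds ratio (OR).** For *n*₁ cases and *n*₀ controls with post-index risks *p*₁ and *p*₀, the probability of rejecting in the direction of the difference is approximately

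Φ[(|*p*₁ − *p*₀| − 1.96·*se*₀) / *se*₁],

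with *se*₀ from the pooled proportion and *se*₁ from the separate proportions. Control risk is 5%.

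| Residual OR | 50 cases, 1:1 | 200 cases, 1:5 |
|---|---|---|
| 1.5 | 7% | 29% |
| 2 | 14% | 67% |
| 3 | 32% | 97% |
| 5 | 66% | about 100% |

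**Step 2: imbalance only in pre-index inpatient status.** If a share *a* of cases and *b* of controls were inpatients in the pre-index window, and post-index risk is *r*₁ with and *r*₀ without that history, then *p*₁ = *a*·*r*₁ + (1 − *a*)·*r*₀ and *p*₀ = *b*·*r*₁ + (1 − *b*)·*r*₀.

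Example: *a* = 0.20, *b* = 0.05, *r*₁ = 0.30, *r*₀ = 0.04.
- *p*₁ = 0.060 + 0.032 = 0.092 and *p*₀ = 0.015 + 0.038 = 0.053.
- OR = (0.092/0.908)/(0.053/0.947) = 1.81.
- With 100 cases and 300 controls, the pooled proportion is (9.2 + 15.9)/400 = 0.06275, *se*₀ = 0.0280 and *se*₁ = 0.0317.
- Φ[(0.039 − 1.96 × 0.0280)/0.0317] = Φ(−0.50) = 31%.

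| Pre-index, cases v controls | Post-index risk with / without history | OR | 50, 1:1 | 100, 1:3 | 200, 1:5 |
|---|---|---|---|---|---|
| 20% v 5% | 15% / 4% | 1.39 | 6% | 11% | 19% |
| 20% v 5% | 30% / 4% | 1.81 | 11% | 31% | 56% |
| 40% v 5% | 40% / 4% | 3.66 | 49% | 93% | about 100% |

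**Step 3: does adding pre-index status repair it?** That depends on how people are selected for a C(E)TR.

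*Selection through recent admission* (simulation, 1:5 controls, 400 replicates):

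| Pre-index, cases v controls | C(E)TRs | Post-only | Plus pre-index status |
|---|---|---|---|
| 57–59% v 6–7% | 40 | 68% | 6% |
| 57–59% v 6–7% | 100 | 96% | 4% |
| 34% v 6–7% | 40 | 30% | 5% |
| 34% v 6–7% | 100 | 62% | 4% |

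*Selection on a stable latent risk* (simulation, 100 cases, 1:3, 600 replicates). Each person has one log-odds of admission for both periods, shifted upward in cases. Control risk is about 8.5%.

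| Case risk | Post-only | Plus pre-index status | DiD |
|---|---|---|---|
| 8.5% (no imbalance) | 4% | 5% | 5% |
| 14% | 36% | 26% | 4% |
| 18% | 71% | 55% | 5% |
| 25% | 98% | 87% | 7% |

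The near-nominal DiD column follows from the set-up, which builds in parallel trends. It does not show that the DiD is unbiased here. The simulations also ignore matching with replacement and repeated events per person.

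**The case against.** **The text is more open than a strict reading allows.** The propensity list is only what is expected to be included, and its governing rule is to condition on baseline variables related to both admission and receipt of a C(E)TR. Pre-index status fits that rule. Group is called an independent variable, not the only one, and the supplement and appendix are not shown. This stands as a limit: pre-index status could still enter. But the article does state the fallback's outcome, exposure and use of scores, and nothing visible requires the baseline outcome.

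**The effect could be small.** A reader might infer that the fallback would usually declare an effect, or is almost certain to give an odds ratio above 1. The documents do not support that. It needs a case count, admission rates and an imbalance that they do not give. With few cases or modest imbalance the rate is well below 50%; in Step 1 it passes 50% only with a residual OR of roughly 2 to 3 or more together with enough cases. Propensity scores that include psychiatric diagnoses may also remove part of the imbalance. Nor can it be said that the fallback fails to tell effect from no effect, because only the no-effect case was examined.

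**The fix is partial.** The Introduction describes selection on judged current risk, which is closer to the latent-risk setting, where 26–87% false positives remain after adjustment. This stands, and it is why the interpretation must change along with the model.

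**A sensitivity analysis addresses indication.** The plan may compare the C(E)TR group with people for whom a C(E)TR was suggested but not shown to have occurred. That is useful, but it is exploratory, offered as one of two options joined by and/or, and does not alter the fallback.

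**The fallback may never be used.** True, but the rule should be settled before anyone knows whether the DiD has failed.

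**Conclusion.** The point holds in a limited form. Followed as written, the fallback discards the outcome's own baseline and is open to confounding by indication, most likely in the direction of C(E)TRs appearing to increase admission. Its false-positive rate can be far above 5%. How far depends on the number of C(E)TRs, the admission rates and the imbalance left after weighting; the article gives none of these, and the assumed inputs span about 5% to nearly 100%. Masking of a real benefit follows from the direction of the bias and was not simulated. Adding pre-index status restores about 5% only where selection acts through prior admission. This should be changed, but it affects a contingency analysis and not the planned DiD itself.

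**What to change.** In the Stage 2 section, state that:
- the fallback logistic regression includes 6-month pre-index psychiatric inpatient status (yes/no) as a covariate;
- the propensity score used for the fallback also includes it;
- the fallback result is reported as an association adjusted for prior admission, not as the causal effect of the C(E)TR or the ATT.

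No new data are needed: all psychiatric inpatient spells are already to be extracted to classify C(E)TRs, and the DiD already uses the pre-period outcome. Because the variable precedes the index date, it cannot be a mediator of that C(E)TR, so it is consistent with the Stage 1 rule on confounders. The cost is one extra parameter and a more cautious claim if the fallback is used.

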### Sensitivity analyses

Sensitivity analyses will be carried out on the causal framework to probe the robustness of the applied model. During the C(E)TR identification process, we will identify patients for whom a community C(E)TR was suggested, where there was no evidence that a C(E)TR did in fact occur. These are to be included in the pool of control patients in our main analysis. Exploratory sensitivity analyses will: (1) Re-assign these patients to the C(E)TR group, and use the date in the record when a C(E)TR was suggested (or soon thereafter) as the index date and/or (2) Directly compare the main C(E)TR group with the ‘C(E)TR suggested’ group.

Some patients may have multiple community C(E)TRs while under follow-up. These will be treated as separate events in the main analysis (if the C(E)TRs are at least 6 months apart). Patients who have multiple C(E)TRs may have a different profile of baseline characteristics than those who receive only one. This may lead to preintervention differences in the C(E)TR versus no C(E)TR groups that cannot be sufficiently controlled for using the propensity scoring method. A sensitivity analysis will be performed on the subgroup of patients who only had one C(E)TR (vs no C(E)TR), improving sensitivity to the causal effect of a single C(E)TR.

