### Classification of C(E)TRs as community or inpatient

Information on all psychiatric inpatient spells will be extracted for those in the cohort. We will place this alongside the dates of recorded C(E)TRs to categorise the C(E)TR as a community C(E)TR (ie, occurring when the person was living in the community) or an inpatient C(E)TR (ie, occurring when the person was admitted to a psychiatric hospital). All analyses that follow will be performed on community C(E)TRs.

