### Index date

The index date will be defined as the date on which a community C(E)TR was held.

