### Matching a control group

We will match between one and five controls, who will not have a community C(E)TR, per patient who has a C(E)TR. Eligibility will be a diagnosis of intellectual disability or autism and having received a continuous period of community care within SLaM services for at least a year between 1 January 2015 and 31 December 2023. Matching will be based on age (±3 years), sex (male/female) and diagnosis (intellectual disability with/without autism, or autism without intellectual disability). Controls should be under an active episode of community care and not be an inpatient on the index date of their matched case. They must also have been under SLaM services for a similar total duration of their matched case (±2 years). Matching with replacement will be applied to ensure every case has an appropriate match according to these criteria. A pseudo-index date for each control will be assigned and will be the same as the index date of their matched case.

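### The exploratory 'C(E)TR suggested' analyses mix two time zeros: with no true effect, option (2) usually favours C(E)TRs and option (1) tends to count against them

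*Protocol article*

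**What the plan says.** All references are to sub-study 1 of the protocol article unless stated.

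- **Index date:** "The index date will be defined as the date on which a community C(E)TR was held".
- **Classification of C(E)TRs as community or inpatient** (common to both sub-studies): a review counts as the exposure only if it took place "occurring when the person was living in the community". A review held during an admission is an inpatient C(E)TR.
- **Sensitivity analyses:** the suggested group consists of patients for whom a community review was raised but "where there was no evidence that a C(E)TR did in fact occur". In the main analysis they belong to the control pool. The text continues "Exploratory sensitivity analyses will" and gives two options joined by 'and/or'. Option (1) moves the suggested-only patients into the exposed group. To fix when their follow-up starts, it would "use the date in the record when a C(E)TR was suggested (or soon thereafter) as the index date". Option (2) is to "Directly compare the main C(E)TR group with the ‘C(E)TR suggested’ group"; no index date is restated for it.
- **Matching a control group:** "A pseudo-index date for each control will be assigned and will be the same as the index date of their matched case".
- **Outcome:** any psychiatric admission in the 6 months after the index date, as a yes/no variable.

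**The concern.** Patients whose review was held enter follow-up at the meeting, after the wait. Suggested-only patients, on the only date given, enter at the suggestion, before any wait. The suggested-only group is also defined by something that happens later. A patient who is an inpatient when the meeting would have fallen cannot have a community review. If no review is then evidenced, that patient is suggested-only, and the admission counts as a post-index event. Admission can therefore both assign the group and be the outcome.

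The wait is unlikely to be negligible: the section on multiple C(E)TRs says these meetings need considerable planning, and the introduction says they are meant for people at high risk of admission.

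The stake is interpretation. The propensity variables expected in Stage 1 are socio-demographic and diagnostic, and matching uses age, sex, diagnosis and time under the service. Suggested-only patients are the one comparator described who share the trigger for a review. A reader would give weight to a comparison with them, so it should not show a difference when there is none.

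**Working it through.** The article gives no admission rate, waiting time or number of events, so there is no figure of its own to reproduce. The check asks what each option would show if C(E)TRs had no effect.

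**Assumed inputs (none from the documents):** constant admission hazard λ per month; fixed wait W months from suggestion to meeting; any admission during the wait cancels the meeting; a share f of the remaining meetings fails for other reasons.

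**Formulas under the null.**
- Held group, 6 months from the meeting: r = 1 − exp(−6λ).
- Admission during the wait: w = 1 − exp(−λW).
- Suggested-only group, 6 months from the suggestion: [f·r + (1 − f)·w] / [f + (1 − f)·w].

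**Option (2), raw 6-month risk.** For λ = 0.05, W = 1, f = 0.30: r = 1 − exp(−0.30) = 0.259 and w = 0.0488. The suggested-only risk is (0.0778 + 0.0341) / (0.30 + 0.0341) = 0.335.

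| λ per month | W (months) | f | Held | Suggested only | Difference (points) |
|---|---|---|---|---|---|
| 0.05 | 1 | 30% | 25.9% | 33.5% | −7.6 (OR 0.69) |
| 0.05 | 2 | 30% | 25.9% | 39.4% | −13.5 (OR 0.54) |
| 0.02 | 0.5 | 50% | 11.3% | 12.2% | −0.9 |
| 0.10 | 2 | 30% | 45.1% | 61.4% | −16.3 |

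A wider grid was simulated and checked against the closed form: 6-month risk 10, 20 or 40%; mean wait 0.5, 1 or 2 months; f of 10, 30 or 60%. The sign was the same in all 27 scenarios, with spurious risk ratios (held/suggested) of about 0.32 to 0.97. The largest difference was about −35 points (risk 40%, wait 2 months, f = 10%). Two variants kept the sign. With stays averaging 2 months, so that some patients are discharged before the meeting, the example with 20% risk, 1-month wait and f = 30% moved from −6.3 to −4.7 points. With the hazard halved after 2 months, risk ratios were 0.44 to 0.78.

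**Option (2), difference-in-differences scale.** In that 20% example, λ = −ln(0.8)/6 = 0.0372. The held group's 6 months before the meeting contain the 1-month admission-free wait, so its pre-period risk is 1 − exp(−5 × 0.0372) = 17.0%. The suggested-only group's pre-period risk is 20.0%. The estimate is (20.0 − 17.0) − (26.3 − 20.0) = −3.3 points. With f = 60% the suggested-only risk is 21.9%, and the estimate is 3.0 − 1.9 = +1.1 points, against C(E)TRs. Over the grid the range is about −25 to +5 points.

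**Option (1).** Suggested-only patients join the exposed group and bring their early admissions. In the 20% example they form 32.6% of it, so its risk is 0.326 × 26.3% + 0.674 × 20.0% = 22.0%, against 20.0% in controls with the same hazard. Over the grid the spurious excess is about 0.3 to 8.4 points, against C(E)TRs.

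**After the fix.** Under the constant-hazard null, two groups taken at the same time since suggestion, both still in the community and not yet reviewed before that point, have the same 6-month risk (risk ratio 1.00). Everyone with a suggestion, followed from the suggestion, also has risk r, equal to that of controls.

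**The case against.** A reader might infer that both options are biased towards C(E)TRs through immortal time, and that the study's causal claim is compromised. The documents do not support that.

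- **Option (1) does not favour C(E)TRs.** Suggested-only patients enter the exposed group, and each control shares its case's index date. Under a constant hazard the bias is in the other direction. The option can also be read as a check on missed meetings, with the suggestion date standing in for an undocumented meeting date.
- **The index date in option (2) is inferred.** The suggestion date is attached to option (1) only, and 'soon thereafter' leaves room for a later start. The other date in the text, the control's pseudo-index date, is unrelated to when the patient's own review was suggested, so it would not align the groups either.
- **The wait is not strictly immortal.** The person must be in the community on the meeting date, not throughout the wait, and the wait is not counted in the held group's follow-up. This is misaligned time zero with selection on a post-baseline event.
- **Some admitted patients may not be in the suggested group.** Those later given an inpatient C(E)TR might not satisfy its definition, which would shrink the bias. The text does not settle this.
- **The planned model is difference-in-differences.** There the bias is smaller and its sign is not guaranteed. The raw-risk figures apply to the fallback logistic regression on post-index status.
- **The analyses are exploratory,** and the article does not offer them as its test of confounding by indication.

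All of these stand and limit the point. None removes the mismatch of starting dates or the fact that admission can define the comparison group.

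**Conclusion.** The point holds for the exploratory analyses only. Time zero is the meeting for held cases and, on the only date given, the suggestion for suggested-only patients, whose group is defined by a later non-event that admission can cause.

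In option (2), read with the suggestion date as index, this creates an apparent benefit on post-index risk when there is none. The size is about −1 to −16 points if 50 to 70% of suggested reviews are held among those still in the community, with hazards of 2 to 10% a month and waits of 0.5 to 2 months. It is larger if few meetings fail for reasons other than admission. On the planned difference-in-differences scale the bias usually favours C(E)TRs but can reverse. In option (1) the bias runs against C(E)TRs under a constant hazard. All sizes rest on assumed rates and waits. The primary estimate is not directly affected. The correction is worth making because these analyses are meant to probe the robustness of the causal model, and neither option is a clean check as written.

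**What to change.** 1. During the planned record review, also record the date of the first documented suggestion for patients whose review was held, and replace 'soon thereafter' with a defined rule.
2. For option (2), match each held review to patients with a documented suggestion who, at the same time since suggestion, are still in the community and not yet reviewed, and start both at that point. Choose comparators by their status on that date, not by whether a review ever followed. Moving the held group's index back to the suggestion while still grouping by whether a meeting later took place would not do: that would create true immortal time.
3. For option (1), index the whole combined group at the suggestion date and assign control pseudo-index dates to match.
4. State whether patients admitted while waiting and then given an inpatient C(E)TR belong to the suggested group.

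The cost is one extra date field. The article commits to extracting meeting dates, not suggestion dates for held cases, so held cases with no recorded suggestion would drop out of these exploratory analyses. Their number is unknown and should be reported.
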